### Statistical Analysis

#### Power

On the basis of previous psychosocial intervention studies with a similar population at our recruitment site, we expect an attrition rate of 20% for the participants with SSD [44,45]. Thus, for a targeted sample of 20 participants, the inclusion of a maximum of 4 additional participants should be expected, leading to 24 participants with SSD. This sample size will allow us to determine potential barriers for remote RC2S, improve the protocol and the adapted versions, determine the preliminary effects of the treatment, and obtain sufficient data to compute effect sizes for statistical power analyses in a future efficacy study. Although no stratification for gender and language will be applied, we aim, as much as possible, to recruit 10 English speakers and 10 French speakers, and we aim to have a proportion of men and women that is consistent with what is observed clinically.

As for the therapists, we aim to recruit 5 participants to obtain a variety of perspectives.

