#### Data Analysis

To assess the acceptability, feasibility, safety, and implementation of remote North American English and French-Canadian versions of RC2S, descriptive statistics will be used to summarize the objective indicators and the quantitative answers from the questionnaires (eg, number of missed sessions). Open-ended questions in the RC2S+ Acceptability, Usability, Safety, Impact, and Satisfaction Questionnaire and the Questionnaire on therapists’ perspective will be classified into categories associated with the implementation of remote psychosocial interventions [46,47]. These analyses will notably determine if the participants with SSD and the therapists perceive the remote administration of the culturally adapted versions of RC2S as feasible and acceptable. We will assess the engagement of participants (eg, motivation, number of sessions completed, and number of completers), the perception of the usefulness of the intervention by both participants with SSD and therapists, and the overall satisfaction with the intervention and the delivery mode. This information is necessary to determine if the remote administration of the culturally adapted versions of RC2S is feasible and acceptable before planning an efficacy trial. These results will also provide information to determine if some modifications to the protocol are necessary.

For the objective regarding the preliminary effect of RC2S on primary and secondary outcomes, we will use an intention-to-treat approach, including the data of all participants who entered the study. Effect sizes will be calculated by subtracting scores at baseline from posttest scores and dividing them by the SD of baseline scores for both primary and secondary outcomes. Linear mixed models for repeated measures will be used to assess the effect of RC2S on both primary and secondary outcomes, with fixed effects of time. Gender, language, and the severity of social cognitive impairments will be used as covariates. Although *P* values will be calculated, we will be mostly interested in the effect sizes to guide power analyses for a future efficacy trial.

For other outcomes, including the in-session questionnaires, descriptive statistics will be used to summarize the data for both groups of participants. Motivation toward treatment and perception of therapeutic alliance will be correlated with primary and secondary outcomes, as well as with the objective indicators of feasibility and acceptability.

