## Discussion

### Overview

This study will first provide necessary information regarding the translation and adaptation of RC2S in North American English and French-Canadian. Participants with SSD, therapists, and the members of the research team will be able to test the program to identify any typo or error that might be present in these initial versions of the program. This will be important to correct any issues for a future efficacy trial.

This project will also provide initial information regarding the feasibility and acceptability of remote administration of these new versions of RC2S. Thus, this study will provide the first insights into the positive impacts and challenges of delivering this intervention remotely, which has never been done before. We hope that we will be able to address most of these challenges in a future efficacy trial. Furthermore, the results from this project will provide information regarding the implementation of RC2S in clinical settings. This information is central to documentation in any intervention study, given the significant research-to-practice gap [48] limiting the implementation of interventions developed in the context of research in clinical settings.

Finally, this study will provide preliminary information regarding the effect of the intervention on different outcomes. This type of pilot study is essential to gathering data to guide a future efficacy trial. Among other advantages, the results of this study will provide the data to calculate the effect sizes necessary to determine the required sample size in a future randomized controlled trial assessing the efficacy of RC2S.

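### The stated effect size carries no small-sample correction, so at 20 to 24 participants it runs about 3-4% too large on average

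*Protocol article*

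**What the plan says.** The Data Analysis section of the protocol article gives one formula for all primary and secondary outcomes: "Effect sizes will be calculated by subtracting scores at baseline from posttest scores and dividing them by the SD of baseline scores". It also plans linear mixed models for repeated measures and P values, and it sets the priority among them: "we will be mostly interested in the effect sizes to guide power analyses for a future efficacy trial". The Overview part of the Discussion repeats the purpose, saying that the results will "provide the data to calculate the effect sizes necessary to determine the required sample size in a future randomized controlled trial".

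Two statements determine how many baseline scores stand behind the SD. The Power section says "we expect an attrition rate of 20% for the participants with SSD" and "for a targeted sample of 20 participants, the inclusion of a maximum of 4 additional participants should be expected", "leading to 24 participants with SSD". The Data Analysis section says "we will use an intention-to-treat approach, including the data of all participants who entered the study". So up to 24 baseline scores may enter the SD, with about 20 people completing.

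**The concern.** The numerator of the formula, the mean change, is unbiased. The denominator is a sample SD, and the expected value of one over a sample SD exceeds one over the true SD. The ratio is therefore too large in magnitude on average, whichever direction counts as improvement. The bias shrinks as n grows, but at 20 to 24 people it has not vanished. It acts in the same direction on every outcome, so looking across outcomes does not average it away.

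It matters because the plan ranks effect sizes above P values and intends to carry them into a power analysis. Required sample size varies as one over the effect size squared, so an excess in the effect size is roughly doubled, as a percentage, in the sample size derived from it.

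**Working it through.** **The plan's own figure.** The only sample-size figure is 24 enrolled for a target of 20 with 20% attrition. 20 × 1.2 = 24 reproduces it. Dividing by the retention rate would give 20/0.8 = 25, and 24 × 0.8 = 19.2 completers, so the target is met to within one person. The figure does not rest on a power calculation.

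**Values of n.** 24 is the number of baseline scores if everyone who entered contributes. 20 is the target. 16 = 20 × 0.8 would arise only if no extra participants were enrolled, contrary to the Power section, and only completers' baseline scores were used.

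**Correction factor.** With m = n - 1, the exact factor under normality is J = Γ(m/2) / [√(m/2) Γ((m-1)/2)], closely approximated by 1 - 3/(4m - 1). The upward bias is 1/J - 1. If the average estimate were put straight into a sample-size formula, the shortfall would be 1 - J².

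| n | 1 - 3/(4(n-1) - 1) | J exact | Upward bias | 1 - J² |
|---|---|---|---|---|
| 24 | 1 - 3/91 = 0.967 | 0.967 | 3.4% | 6.5% |
| 20 | 1 - 3/75 = 0.960 | 0.960 | 4.2% | 7.9% |
| 16 | 1 - 3/59 = 0.949 | 0.949 | 5.4% | 9.9% |

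**Simulation.** The documents give neither a true effect nor a pre-post correlation, so both are assumed. With a true value of 0.5, a correlation of 0.7 and 100,000 bivariate normal samples per setting, the mean estimate is 0.517 (n = 24), 0.521 (n = 20) and 0.527 (n = 16), which agrees with the table. Over correlations of 0.5 to 0.8 and true values of 0.3 to 0.8, the simulated bias at n = 20 stays between 4.1% and 4.4%.

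**Bias against sampling error (n = 20, true value 0.5, correlation 0.7).** The estimate has an SD of about 0.20 and a 95% range of 0.16 to 0.96. The bias is 0.02, about one tenth of that SD.

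**What the correction does.** Under normality the mean change is independent of the baseline SD. In baseline-SD units its variance is 2(1 - 0.7)/20 = 0.03.

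- Uncorrected: the expected square is (0.25 + 0.03) × 19/17 = 0.3129. The variance is 0.3129 - 0.5209² = 0.0416. The root mean squared error is √(0.0416 + 0.0209²) = 0.205.
- Corrected: the bias is zero and the root mean squared error is 0.960 × √0.0416 = 0.196.

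**Effect on a future sample size.** Take a two-arm comparison at two-sided 5% and 80% power, with N per arm = 2 × (2.8016/d)². A true d of 0.50 needs 63 per arm. The average uncorrected value at n = 20, 0.521, gives 58. A single realised estimate behaves differently: the N per arm derived from it has a median of 61 and a 95% range of about 17 to 615, and it falls below 63 in 51.5% of samples.

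**The case against.** The strongest case against raising this is that the effect analysis is exploratory, the effect sizes are only meant to guide later planning, and a shift of about 0.02 changes no conclusion of this study. That is fair as to size, and it is why the point is a refinement. It does not remove the point: the formula is stated outright, without the factor, for the quantity that the plan most wants to carry forward.

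Three stronger readings are tempting, and the documents do not support them.

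- A reader might infer that a future trial will be 8-10% too small. The upper end needs n = 16, whereas the Power section plans 24 enrolled for a target of 20. Even the 6-8% that follows from 20 to 24 people is arithmetic on the average estimate. One realised estimate gives a planned size that is too small or too large with nearly equal chance, and its median is only about 3% low (61 against 63 per arm).
- A reader might infer that the plan omits confidence intervals, or offers only P values beside the effect sizes. The article neither mentions nor excludes an interval, and that detail is commonly left to the analysis plan or the report. It also plans mixed models, which yield an estimated change with a standard error.
- A reader might take the corrected value as a sound input for sizing a randomised trial. The Limitations section states that there is no control group and that this limits what can be said about preliminary effects. Multiplying by 0.96 does not change that.

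**Conclusion.** The point holds as a minor one. The stated formula is an uncorrected standardised mean change and is too large on average by about 3.4% with 24 baseline scores and 4.2% with 20, or 5.4% if only 16 contributed. These percentages depend only on n and on approximate normality of the baseline scores; on bounded scales they are approximate. The statements about sampling error, mean squared error and future sample size rest in addition on an assumed true value of 0.5 and an assumed pre-post correlation of 0.7. Under those assumptions sampling error is about ten times the bias. The correction is therefore worth making because it is free, not because the bias is the main uncertainty in the estimate.

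**What to change.** In the Data Analysis section, add that each standardised change will be multiplied by 1 - 3/(4(n-1) - 1), and define n as the number of baseline scores used for the SD. If the SD uses everyone who entered and the mean change uses completers, n is the former. State the n for each outcome.

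It is also advisable to report a 95% confidence interval with each effect size, so that whoever plans the next trial sees the imprecision and not just one value. This is a recommendation and does not correct an error.

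The cost is one multiplication per outcome and effect sizes that are 3-4% smaller as reported. Recruitment, data collection and participants are unaffected.

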		**Penn Emotion Recognition Task [29]**				
			Emotion recognition	Baseline, posttest		

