		**Working Alliance Inventory-Short form [41]**				
			Therapeutic alliance in RC2S	Sessions 5, 11, and 23		

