**Figure 1 figure1:**
[figure not shown]
Description of RC2S (Remédiation Cognitive de la Cognition Sociale dans la Schizophrénie) sessions.

During the first 2 sessions of therapy, a case formulation is elaborated to identify the strengths, weaknesses, and CR goals. Psychoeducation about social cognition and the impact of social cognitive impairments on functioning is presented. To complement the objective assessment of social cognition performed at baseline, the functional impacts of social cognitive impairments are assessed with the Échelle de répercussions fonctionnelles des troubles de la Cognition Sociale (ERF-CS; *Scale for the assessment of functional impacts of social cognitive deficits*) [38]. This semistructured interview explores the presence and impact of various social cognitive impairments in daily life. The interview also assesses how much the participant is bothered by these impairments. The results from the ERF-CS provide a detailed perspective on how social cognitive impairments disrupt the participant’s life. Furthermore, given the psychometric limitations of most available social cognitive tasks, particularly regarding the ecological aspect of these tasks, the ERF-CS provides in-depth and concrete information to build a case formulation and support the client while creating treatment objectives. In this project, treatment objectives will be developed with the Goal Attainment Scale (GAS) [28], a flexible scale that allows the elaboration of personalized objectives before starting treatment, with a reassessment at the end of therapy. The GAS is rated on a scale from −2 to +2. A score of 0 indicates that the participant has reached their initial goal. Scores of +1 or +2 are obtained if the participant has exceeded or greatly exceeded their initial goal. Scores of −1 and −2 are obtained if the participant did not completely reach their objective. When the objectives are set, an operational definition is established for each level of rating.

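### Correlations of motivation and alliance with the outcomes name no use of the pre-treatment score, which is collected for every outcome except goal attainment

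*Protocol article*

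**What the plan says.** The last paragraph of Data Analysis states that "Motivation toward treatment and perception of therapeutic alliance will be correlated with primary and secondary outcomes", and also with the feasibility and acceptability indicators. It does not say whether the outcome enters as a posttest score, a change or a baseline-adjusted value.

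The only covariates are named one paragraph earlier, straight after the mixed-model sentence: "Gender, language, and the severity of social cognitive impairments will be used as covariates". None of them is the outcome's own starting score. That paragraph also defines the pre-post effect: "Effect sizes will be calculated by subtracting scores at baseline from posttest scores and dividing them by the SD of baseline scores".

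Table 1 gives the timing. The social cognition tests and most secondary scales are measured before and after treatment, for example "Emotion recognition Baseline, posttest". The ERF-CS is given at sessions 1 and 24. The ratings come later than baseline: "Therapeutic alliance in RC2S Sessions 5, 11, and 23", with the same sessions for motivation.

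The Goal Attainment Scale differs. Goals are set at the start and rated from -2 to +2 against the participant's own target: "A score of 0 indicates that the participant has reached their initial goal".

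**The concern.** Motivation and alliance are observed during therapy, so they may depend on how impaired or symptomatic a participant was at the start. The protocol makes this plausible. Entry requires a subjective or objective impairment in only one domain, so starting scores on any given test can vary widely. The exercises, their difficulty and the number of sessions per domain are then tailored to baseline impairment, so starting level shapes the therapy being rated.

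A posttest score carries the starting level forward. If ratings track starting level, they will correlate with posttest even when they have nothing to do with response. A change score does not solve this: those who start low tend to gain more through regression to the mean, which pushes the correlation the other way. The sign of a spurious association would then depend on a choice that the sentence does not state.

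This is the only stated analysis linking motivation and alliance to clinical outcomes, in a study meant to inform a later efficacy trial. The plan's preference for effect sizes over P values does not help, because the bias is in the correlation itself.

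**Working it through.** **Inputs from the protocol.** The target is 20 participants with SSD (Recruitment). The Power section allows 20% attrition: 20 + 0.20 × 20 = 24, which reproduces its figure; 24 × 0.80 = 19.2 would remain, so n = 20 is used below. No alpha, power or target correlation is stated for these correlations, so there is no plan figure for them to reproduce.

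**Assumed inputs.** Two-sided 5% level; correlation of rating with baseline a = 0, 0.3 or 0.5; correlation of baseline with posttest r = 0.3 to 0.8; equal variances at both times; outcomes scored so that higher is better.

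**Step 1: bias when the rating has no link to posttest beyond baseline.**

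- Posttest correlation = a × r.
- Change-score correlation = (ar − a)/√(2 − 2r) = −a(1 − r)/√(2 − 2r).
- Partial correlation given baseline = 0.

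For example, with a = 0.5 and r = 0.5: posttest 0.5 × 0.5 = 0.25; change −0.5 × 0.5/√1 = −0.25. Rejection rates are from simulation (n = 20, 40,000 replicates per scenario).

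| a | r | Posttest: expected r (rejects) | Change: expected r (rejects) | Partial: rejects |
|---|---|---|---|---|
| 0.3 | 0.5 | +0.15 (9.8%) | −0.15 (9.6%) | 5.0% |
| 0.3 | 0.7 | +0.21 (14.4%) | −0.12 (7.7%) | 4.9% |
| 0.5 | 0.5 | +0.25 (18.9%) | −0.25 (18.6%) | 5.1% |
| 0.5 | 0.7 | +0.35 (33.6%) | −0.19 (13.0%) | 4.8% |

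Over the wider range r = 0.3 to 0.8, false-positive rates are 6.5% to 43.4% for posttest and 6.6% to 24.9% for change. At a = 0 both biases vanish and all three methods reject about 5% of the time.

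**Step 2: precision when the rating is unrelated to baseline (a = 0).** With a true standardised slope of 0.4, adjustment removes the share r² of posttest variance, and the partial correlation is 0.4/√(1 − r²).

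| r | True partial correlation | Power: posttest | Power: change | Power: partial |
|---|---|---|---|---|
| 0.3 | 0.42 | 43% | 32% | 45% |
| 0.5 | 0.46 | 43% | 43% | 53% |
| 0.7 | 0.56 | 43% | 67% | 74% |
| 0.8 | 0.67 | 43% | 88% | 91% |

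Against the posttest correlation the gain is 2 points at r = 0.3 and 10 or more from r = 0.5.

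**Step 3: both at once.** With a = 0.3, r = 0.5 and the same slope of 0.4, the posttest correlation rejects in 67% of trials and the partial in 49%. The excess reflects bias, so Step 2 cannot be carried over to the setting of Step 1.

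**Step 4: limit of the remedy.** The zero in Step 1 holds because the simulated posttest depends on the observed baseline. Suppose instead that true severity drives both rating and posttest, and that the baseline test has reliability 0.7 (assumed). The unadjusted posttest correlation is then ar/0.7, and the partial correlation is (ar/0.7 − ar)/√((1 − a²)(1 − r²)).

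- a = 0.3, r = 0.5: unadjusted 0.15/0.7 = 0.21; partial 0.064/0.826 = 0.08.
- a = 0.5, r = 0.7: unadjusted 0.35/0.7 = 0.50; partial 0.15/0.618 = 0.24.

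Adjustment more than halves the bias but does not remove it.

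**The case against.** The strongest reply is that this reads silence as a decision. The article says only that the variables will be correlated; it does not exclude a partial correlation, and a condensed article may leave the form of the score to the fuller plan. That stands in part: the absence of adjustment is inferred. It does not dispose of the point, because the method named is a correlation, adjustment is mentioned only for the mixed models, and both plain readings of the sentence are open to the same confounding.

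A reader might infer that participants who started out less impaired will show up as a positive alliance or motivation effect. The text does not support that direction: it holds for posttest scores and reverses for change scores, and the plan's own effect size is a change.

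A reader might also infer that power is simply lost. That is true against a posttest correlation only when ratings are roughly unrelated to baseline and baseline predicts posttest. In the confounded case of Step 3 the plain correlation rejects more often.

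Nor does the point reach every outcome, since goal attainment is scored against a personal target.

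Other replies also stand. All the correlations are assumed. Baseline adjustment cannot deal with ratings at sessions 11 and 23 that follow improvement already made. The effect objective is exploratory, no objective is stated on engagement and benefit, and what the study hands to the next trial for sample size is the pre-post effect sizes.

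**Conclusion.** The point holds as a low-cost improvement to an exploratory analysis. As worded, the correlations make no stated use of pre-treatment scores that the study collects for every primary and secondary outcome except goal attainment. If ratings correlate 0.3 to 0.5 with baseline and baseline correlates 0.5 to 0.7 with posttest, a null association would appear as about +0.15 to +0.35 with posttest scores or −0.12 to −0.25 with change scores. If ratings are unrelated to baseline, nothing is biased and the case for adjustment is precision: negligible over a posttest correlation at r = 0.3, material from 0.5. Which situation applies cannot be known from the document. The pre-post effect sizes and the mixed models are not affected.

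**What to change.** Replace the plain correlation in the last paragraph of Data Analysis with wording such as: *For each primary and secondary outcome with a pre-treatment score (baseline, or session 1 for the ERF-CS), the association with motivation and with alliance will be the partial correlation between the rating and the post-treatment score given that pre-treatment score (equivalently, a regression of the post-treatment score on the pre-treatment score and the rating), with a 95% confidence interval. Goal attainment will be correlated without adjustment. These are exploratory associations; adjustment reduces but does not eliminate confounding when baseline is measured with error or when later ratings follow improvement.*

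Correlations with the feasibility and acceptability indicators can stay as they are. The cost is one degree of freedom per correlation: at n = 20 the Fisher-z half-width of the interval goes from 1.96/√17 = 0.475 to 1.96/√16 = 0.490. No new data, visits or staff are needed.
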